### Procedure for unblinding if needed {17b}

Unblinding is possible in emergent clinical situations by opening the sealed envelope with drug code and blinding information inside, which will be available to medical doctors in the cardiac surgery ward 24 h per day. If the respective sealed envelope is opened (unblinded) for any reason, the patient will automatically be dismissed from the clinical trial.

## Data collection and management

### Plans for assessment and collection of outcomes {18a}

Different outcome investigators are responsible for data collection and assessment (trial examiners, trial clinical biochemist, trial clinical radiologist, trial pharmacists, and trial administrative workers).

There are two electronic databases: Database No. 1 (central trial register) with access for all trial workers except the pharmacist, and Database No. 2 (information about IMP content) with an access restricted to the pharmacist and independent clinical pharmacist.

Trial data from laboratory tests will be copied from hospital patient medical records and stored in one database (Database No. 1) at the end of the clinical trial.

Two paper questionnaires will be used: Questionnaire No. 1 for medical doctor reporting clinical findings and Questionnaire No. 2 for the trial participants. Patient questionnaires and medical assessment questionnaires will primarily be hard copy (paper version), and the data from them will be manually transferred to the central electronic database.

The main clinical trial coordinator is also responsible for clinical trial monitoring.

### Plans to promote participant retention and complete follow-up {18b}

There are no extra plans to promote participant retention. Trial participants have no financial reward for participating in the clinical trial. Automatic SMS reminders for trial medication and all medical appointments are introduced. Patients will return completed patient questionnaires (confirming all medication administrations) at the end of the clinical trial. Complete follow-up will be made by the clinical trial coordinator by telephone.

### Data management {19}

Data are recorded to the trial database and partially to the participant’s protocol (paper form), stored in the corresponding author’s office.

### Confidentiality {27}

Trial data are collected in a shared trial database. The authors of the trial have access to this database only. The database can only be opened via the hospital local network.

### Plans for collection, laboratory evaluation, and storage of biological specimens for genetic or molecular analysis in this trial/future use {33}

All biological specimens are collected and stored according to standard GCP and GLP guidelines. No future use in ancillary studies is planned; therefore, no long-term storage is necessary.

## Statistical methods

### Statistical methods for primary and secondary outcomes {20a}

In the statistical analysis of the primary endpoint, it will be necessary to ascertain whether the incidence of all sternotomy complications (6 months follow-up) differs significantly between the treatment and placebo groups. Data will be expressed as number of patients with or without sternotomy healing complications in the placebo/cholecalciferol groups. The chi-square test will be used for this analysis.

Data of all secondary endpoints will be expressed as arithmetic average ± standard deviation. To analyze these data, a two-group *t* test will be used.

This clinical trial assumes a significance level of 0.05. The software MedCalc (version 17.8.6.) will be used for statistical calculations.

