### Recruitment {15}

Males and females 18 to 95 years of age who fulfill the indication criteria for undergoing cardiac surgery by a standardized scoring system (EUROSCORE) can participate in our clinical trial (CT), if they meet the eligibility criteria below (see Table 2). Subjects that are pregnant, breastfeeding, or planning to become pregnant during CT will be excluded. If a subject becomes pregnant during the CT, they will be terminated from the CT medication and will be removed from CT. However, due to the character of the clinical trial and the medication used, it will not be necessary to require women to use contraceptives.

Patients will be admitted to the CT independent of age, gender, race, and type of surgery including sternotomy. Subsequently, initial calcidiol blood concentration will be evaluated for each proposed patient. If the calcidiol blood concentration is below 75 nmol/L, the patient will be offered participation in the CT. By providing signed, informed consent, the patient will become a subject of CT assessment, will receive a CT identification number, and will be subsequently randomized (see Fig. 1).

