## Assignment of interventions: allocation

### Sequence generation {16a}

Sequence allocation from number 1 up to number 600 was done using R Core Team randomization software (version 2015) with the accompanying information of whether the respective subject receives a placebo or cholecalciferol. The probability that respective identification number is assigned to placebo or cholecalciferol was set within the ratio of 1:1 (in blocks) to ensure approximately even distribution of both compounded investigational medicinal products (placebo/cholecalciferol) in both CT arms.

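### The secondary endpoints are fixed to an unadjusted t test although prognostic baseline data are known before randomisation; the comparison is valid but gives up precision

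*Protocol article*

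**What the plan says.** Under *Statistical methods for primary and secondary outcomes {20a}* the article sets one analysis for every secondary endpoint: "Data of all secondary endpoints will be expressed as arithmetic average ± standard deviation", followed by "To analyze these data, a two-group *t* test will be used". The same section adds "This clinical trial assumes a significance level of 0.05". It names no covariate, stratum or model, and no other section supplies one for these endpoints.

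The endpoints concerned (*Secondary endpoints* under *Outcomes {12}*) are the CT sternal healing grade on a 6-point scale, ICU days with mechanical ventilation, total ICU days, readmissions for sternotomy complications, and days of treatment for pericardial or pleural effusion.

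Three other sections bear on the point:

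- *Recruitment {15}*: "Patients will be admitted to the CT independent of age, gender, race, and type of surgery including sternotomy". Patients are aged 18 to 95 and must "fulfill the indication criteria for undergoing cardiac surgery by a standardized scoring system (EUROSCORE"). The section also says "Subsequently, initial calcidiol blood concentration will be evaluated for each proposed patient", and this comes before consent and randomisation.
- *Sequence generation {16a}*: the allocation probability "was set within the ratio of 1:1 (in blocks"). No stratification factor is given, and *Concealment mechanism {16b}* says there were no further restrictions.
- *Methods for additional analyses {20b}*: baseline calcidiol defines three subgroups, for the primary endpoint only.

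**The concern.** Days in ICU, days on ventilation and days of effusion treatment can be expected to vary with age, preoperative risk and type of operation, and the trial deliberately mixes all of these. The article's own rationale cites a large German cardiac surgery study in which low calcidiol went with more ventilation days, which is one of the secondary endpoints. A t test leaves all of that between-patient variation in the error term. Stratified randomisation could have removed part of it, but none is described.

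At stake is the width of the confidence intervals for the recovery endpoints and the chance of detecting a real difference. No sample size or power is stated for any of them, so whatever precision they have comes from a trial sized on the primary endpoint.

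This is separate from whether a t test suits skewed, ordinal or sparse data. Replacing it with another unadjusted test would leave the loss of precision in place.

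**Working it through.** **The plan's own figure.** The only sample-size figure is 284 per arm, for the primary endpoint (*Sample size {14}*: 5% v 1%, α 0.05, power 80%). The two-sided formula without continuity correction is

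n = [z₀.₉₇₅·√(2·p̄·q̄) + z₀.₈₀·√(p₁q₁ + p₂q₂)]² / (p₁ − p₂)²

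With p̄ = 0.03 this is [1.960·√0.0582 + 0.842·√0.0574]² / 0.04² ≈ 284.3, so 284 is reproduced within rounding. (The one-sided version, which the text names, gives 224. That is a separate matter.) Nothing comparable exists for the secondary endpoints, so their gain from adjustment must be shown on assumptions.

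**Inputs**

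- From the article: about 300 per arm; significance level 0.05, taken here as two-sided.
- Assumed: R², the share of outcome variance explained by baseline covariates, from 0.02 to 0.40. The documents give no value.
- Assumed: a true effect for which the unadjusted t test has exactly 80% power.

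**Step 1. Reference effect.** In SD units the unadjusted standard error is √(2/300) = 0.0816. The effect with 80% power is (1.960 + 0.842) × 0.0816 = 0.229 SD.

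**Step 2. Effect of adjustment in a linear model.** The standard error is multiplied by √(1 − R²). Power becomes Φ[2.802/√(1 − R²) − 1.960]. The unadjusted trial of equal precision needs 300/(1 − R²) per arm.

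| Assumed R² | Fall in standard error | Power at 0.229 SD | Equivalent unadjusted n per arm |
|---|---|---|---|
| 0.02 | 1% | 80.8% | 306 |
| 0.05 | 2.5% | 82.0% | 316 |
| 0.10 | 5% | 84.0% | 333 |
| 0.20 | 11% | 87.9% | 375 |
| 0.30 | 16% | 91.8% | 429 |
| 0.40 | 23% | 95.1% | 500 |

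**Step 3. Skewed outcome.** A simulation (2,000 runs, 300 per arm) used a log-normal outcome with log-scale SD 0.8, a treatment shift of −0.2 on the log scale and one prognostic covariate. The outcome was analysed untransformed by linear regression with and without the covariate.

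| Covariate correlation (log scale) | Mean model R² | Power unadjusted | Power adjusted | Gain |
|---|---|---|---|---|
| 0.30 | about 0.08 | 73.8% | 76.3% | 2.5 points |
| 0.45 | about 0.16 | 72.9% | 79.6% | 6.7 points |

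Skewness reduces what a linear covariate can explain: squared log-scale correlations of 0.09 and about 0.20 become about 0.08 and 0.16 on the raw scale, and those R² values also include the treatment term.

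**The case against.** The strongest objection is that nothing here is an error. An unadjusted comparison of randomised arms is valid, the sections do not contradict one another, and no power is claimed for a secondary endpoint. That stands, and it limits the point to efficiency. It does not remove it: the article names one covariate-free test for all these endpoints, so the choice is fixed and not left to a later analysis plan.

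The size is also assumed. At R² = 0.02 the gain is under one point, and calcidiol alone may explain little because enrolment is restricted to below 75 nmol/L. Table 2 excludes repeat sternotomy and several other conditions, which narrows the case mix. Both stand.

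Data access is less certain than it may look. EuroSCORE appears only in connection with the surgical indication, and neither Table 3 nor *Plans for assessment and collection of outcomes {18a}* lists EuroSCORE or operation type as trial data. They may have to come from hospital records.

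Four stronger readings are tempting but unsupported:

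- *That the results would be biased.* Chance imbalance is already reflected in the t test's standard error. As an illustration, suppose one dosing cohort differed from the rest by 0.3 SD (assumed). A 5-point imbalance in its share would then move the estimate by 0.3 × 0.05 = 0.015 SD, against a standard error of 0.082 SD.
- *That the probability of a cohort imbalance can be computed from the German study's shares.* Its lowest band is below 30 nmol/L, whereas the trial's lowest dosing cohort is 0–24 nmol/L. The documents give no share for the latter.
- *That baseline data are ignored altogether.* Calcidiol does define subgroups of the primary endpoint.
- *That the primary endpoint also needs an adjusted model.* At the planned rates there would be about 15 + 3 = 18 events among 600 patients, too few for a useful gain.

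**Conclusion.** The point holds as a loss of precision on the secondary endpoints, not as a threat to validity. If baseline covariates explain 10–30% of the variance, the standard error would fall by 5–16%, and a comparison with 80% power would reach 84–92%. Over the wider range of 2–40% it would reach about 81–95%. Gains are likely to be smaller for skewed day counts, as the simulation shows. All of this rests on an assumed R², an assumed effect size and a linear model; none of these can be checked from the documents.

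The case is strongest for ICU, ventilation and effusion-treatment days. It is weaker for the ordinal CT grade, where √(1 − R²) does not apply directly, and weakest for readmissions, which may be sparse. The change is worth making because it is cheap, but the article's unadjusted analysis would still give an interpretable answer.

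**What to change.** Amend *Statistical methods {20a}* before unblinding:

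1. For ICU days, ventilation days and effusion-treatment days, prespecify a regression model with treatment, baseline calcidiol dosing cohort, age and EuroSCORE. Add operation type if it can be retrieved from hospital records. Report the adjusted difference with its 95% CI.
2. State that the calcidiol cohort is the one used to set the weekly number of drops, because the subgroup section draws its boundaries slightly differently.
3. Apply the same covariates to the CT healing grade where feasible, in a model suited to an ordinal scale.
4. For readmissions, keep covariates to a minimum or omit them.
5. Leave the primary chi-square comparison without an added covariate-adjusted model.

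The cost is analysis wording, some extra analysis work, and extraction of EuroSCORE and operation type if they are not in the trial database. Where a non-linear model is chosen, the adjusted effect is conditional on the covariates and is not the same quantity as the crude difference; the plan should say which is reported. No new visits or patients are needed, and treatment does not change.

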### Interim analyses {21b}

The only trial intervention is based on vitamin D supplementation, so there is no presupposition for harmful effects on trial participants; therefore, no interim analyses and termination decision-making are planned within the trial period.

Rules for terminating trial participation:
Decision by the trial subjectAny subject may elect to withdraw from the clinical trial at any time, without providing a reason. In the case of this decision, the participant will be asked to:
Return the rest of the IMP to Na Homolce Hospital, Cardiac Surgery.Appear within 14 days from the announcement of withdrawal from the clinical trial at the Department of Cardiac Surgery for evaluation of serum calcidiol and calcium (these examinations may also be requested by a general practitioner at the place of the participant’s residence).Decision by the examinerDue to the fact that the clinical trial is based on the administration of physiological vitamin D or placebo, termination of the trial on the part of the investigator is very unlikely. Nevertheless, in the rare circumstances described below, the examiner may elect to exclude a participant from the trial due to preventive reasons.

Criteria for CT interruption by examiners:
IMP intoleranceHypercalcemia—serum total calcium concentration higher than 2.75 mmol/L, measured in at least one of the prescribed examinationsHyperphosphatemia—concentration of total serum phosphorus above 1.61 mmol/L, measured in at least two of the prescribed examinationsIncreased serum alkaline phosphatase activity above twice the reference range, measured in at least two of the prescribed testsA high level of calcidiol above 200 nmol/L, measured in a targeted manner in case of suspected overdose at any time during the trialThe need to use unauthorized medicationPregnancy

Interruption or termination of the trial for other reasons is always subject to appraisal of the examining physician, but due to the trial character and design is not expected.

### Methods for additional analyses (e.g., subgroup analyses) {20b}

Additional subgroup analyses are planned of the primary endpoint in groups with different initial calcidiol concentrations. Three subgroups will be evaluated: 1st with initial calcidiol concentration ≤ 25 nmol/L, 2nd with initial calcidiol concentration > 25 nmol/L and ≤ 50 nmol/L, and 3rd with initial calcidiol concentration > 50 nmol/L. The chi-square test will be used for this analysis.

Another subgroup analysis of the primary endpoint will be focused on sternotomy complication type: presternal, sternal, and retrosternal.

### Methods in analysis to handle protocol non-adherence and any statistical methods to handle missing data {20c}

Any missing data will be explained. Multiple imputations of missing outcome data will be used for sensitivity analyses.

If there are missing data regarding to primary endpoints, the trial participant will be excluded from the final trial evaluation.

If there are missing data from the secondary outcomes, the isolated missing value will be not used for the final trial evaluation.

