#### Sternotomy healing and its complications

Complication rates for median sternotomy range from 0.5 to 5%; however, mortality rates from complications are variable (7–80%). Complications may affect the presternal (cellulitis, sinus tracts, abscess), sternal (osteomyelitis, dehiscence), or retrosternal (mediastinitis, hematoma, abscess) compartments [15]. According to previous studies, superficial complications occurred in 1.1–6.7% of patients, whereas the incidence of deep sternal wound complications ranged from 0.1 to 3.7% [16–18]. In another single-center study with 1279 patients, 76 patients (5.8%) developed sternal wound complications, superficial healing disorders occurred in 43 patients (3.3%), while 33 patients (2.5%) developed deep wound complications [19].

For the purposes of this clinical trial, sternotomy healing complications within the trial are defined as follows:
Presternal complications—an infective or non-infective complication affecting the superficial soft tissues occurring at any time during the clinical trial, not affecting the sternum or mediastinum.Sternal complications—an infective or non-infective complication affecting the sternum (resulting in partial or complete sternal dehiscence or instability), occurring at any time during the clinical trial.Retrosternal complications—an infective or non-infective complication affecting the mediastinal tissues occurring at any time during the clinical trial.

The optimal length of the sternum healing is, per se, the subject of debate. According to one study published in 2014, the sternum is not fully recovered after 3 nor after 6 months [20]. In this clinical trial, a 6-month period for evaluation was selected due to the high probability of capturing any sternotomy healing complications related to bones and soft tissues during the trial.

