### Criteria for discontinuing or modifying allocated interventions {11b}

No interventions or drug dose changes will be made during the trial. If there is any problem related to the clinical trial, patient participation in clinical trial will be terminated. The decision for termination can be made from both sides:
Patient decisionA trial participant may leave the trial at any time without providing a reason.Examiner decisionDue to the fact that the clinical trial is based on the administration of cholecalciferol or placebo, termination of the clinical trial by the investigator is very unlikely. Nevertheless, in rare circumstances described below, the examiner may decide to exclude a subject from the trial due to preventive reasons.

Criteria for the clinical trial discontinuing by examiner:
Cholecalciferol intoleranceHypercalcemia—serum total calcium concentration higher than 2.75 mmol/L, measured in at least one of the scheduled laboratory testsHyperphosphatemia—concentration of total phosphorus in the serum above 1.61 mmol/L, measured in at least two of the scheduled laboratory testsAn increased serum alkaline phosphatase activity two times higher than the physiological range, measured in at least two of the scheduled laboratory testsA high level of calcidiol above 200 nmol/L, measured in a targeted manner in case of suspected overdose at any time during CTThe need to use prohibited medicationPregnancy

Interruption or termination of CT for other reasons is always subject to the judgment of the examiner (medical doctor), but due to its design is not expected.

In both decisions of this participant’s termination, trial subject will be asked to do the following:
To return the rest of the IMP at the hospital Cardiac Surgery DepartmentTo be medically examined within 14 days from the medication withdrawal (calcidiol concentration, calcium concentration)—these examinations can also be requested by a general practitioner in the place of trial subject residence

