#### Prohibited concomitant medication during the clinical trial

Systemic immunosuppressive pharmacotherapy (including corticotherapy) more than 14 days in duration or exceeding the length of hospitalization (if the actual duration of treatment could not be determined), or local corticotherapy applied at the site of wound healing more than 5 days duration.Systemic pharmacotherapy with digitalis cardioactive glycosides at any dosage if not possible to ensure regular monitoring of calcium with a minimum measurement interval of once per week, always before the administration of IMP.Systemic pharmacotherapy with hydrochlorothiazide at a dose higher than 12.5 mg/day if not possible to ensure regular monitoring of calcium with a minimum measurement interval once per week, always before the administration of IMP.Chronic treatment with teriparatide.Chronic treatment with bile acid sequestrant.Chronic treatment with vitamin D or its derivatives (alphacalcifediol, calcitriol, paricalcitol) including ergocalciferol (vitamin D2) in addition to IMP.Administration of any medicinal products or food supplements containing any calcium salt in any dosage if not possible to ensure regular monitoring of calcium with a minimum measurement interval of once every 2 months, always before the administration IMP.

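### The missing-data, unblinding and stopping rules together can remove randomised patients from the primary comparison for reasons that may relate to treatment or outcome

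*Protocol article*

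**What the plan says.** Four parts of the protocol article act together.

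- **Missing data (20c).** "If there are missing data regarding to primary endpoints, the trial participant will be excluded from the final trial evaluation". The same section adds: "Multiple imputations of missing outcome data will be used for sensitivity analyses". The primary analysis is therefore complete-case.
- **Unblinding (17b).** "If the respective sealed envelope is opened (unblinded) for any reason, the patient will automatically be dismissed from the clinical trial".
- **Stopping (11b, repeated in substance in 21b).** "If there is any problem related to the clinical trial, patient participation in clinical trial will be terminated". The listed grounds are intolerance, hypercalcaemia, hyperphosphataemia, raised alkaline phosphatase, calcidiol above 200 nmol/L, need for prohibited medication, and pregnancy. For these, "the examiner may decide to exclude a subject from the trial due to preventive reasons". Prohibited medication includes "local corticotherapy applied at the site of wound healing more than 5 days duration".
- **After leaving (11b, 21b).** The patient is asked to return the remaining study drug and to have calcidiol and calcium checked within 14 days, possibly through a general practitioner. The later sternotomy examinations are not on this list.

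The primary endpoint (section 12) is assessed at 6 weeks and 6 months, and its conditions can be met at any time in the trial. The same section classes patients who do not meet both conditions as free of complications. Replacement of randomised patients is not allowed (16c).

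**The concern.** A patient who is unblinded or stopped before month 6 has no planned second wound assessment. That patient is then likely to lack primary data and to fall under the exclusion rule in 20c. The article nowhere says that such patients stay in follow-up or are analysed in their allocated arm.

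Some of the triggers are unlikely to be neutral. Hypercalcaemia and high calcidiol are plausibly more frequent on cholecalciferol. Prolonged steroid use at the wound and emergency unblinding plausibly occur in patients who are healing badly or are very ill. If exclusions differ by arm and also relate to complication risk, the comparison of those who remain is no longer protected by randomisation. An imputation reported only as a sensitivity analysis leaves the headline result as it is. With a rare endpoint, the status of a handful of patients can decide the trial.

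**Working it through.** **Inputs.** From the sample size section: 5% versus 1%, α = 0.05, power 80%, 284 needed and 300 enrolled per arm. From 20a: chi-square test. The article gives no rate of stopping, unblinding or missing data, so every loss below is an assumption.

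**1. The plan's own figure.** With pooled rate 0.03 and a two-sided test:

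n = [1.960·√(2·0.03·0.97) + 0.842·√(0.05·0.95 + 0.01·0.99)]² / 0.04² = 284.3

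This is 285 when rounded up, against 284 stated, so the figure reproduces as a two-sided calculation. The article calls it one-sided, and the same formula one-sided gives 224; that is a separate point.

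**2. Room for exclusions.** (300 − 284)/300 = 5.3% per arm.

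**3. Expected events.** 300 × 0.05 = 15 on placebo and 300 × 0.01 = 3 on cholecalciferol. Pearson chi-square = 0.04² / [0.03·0.97·(2/300)] = 8.25, p = 0.004.

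**4. Sensitivity to a few patients.**
- Five placebo patients with events removed: 10/295 (3.4%) versus 3/300 (1.0%). Pooled rate 13/595 = 0.0218, chi-square = 3.97, p = 0.046.
- A sixth removed: 9/294 versus 3/300, p = 0.074.
- In the other direction, if 15 versus 3 were observed but four more events lay among removed cholecalciferol patients, the full comparison would be 15 versus 7, p = 0.08.

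**5. Direction of bias (assumed shares).** Suppose there is no true effect, 5% in both arms, and 5% of event-free patients are excluded in each arm (285 × 0.95 = 270.75 remain). Exclude 10% of placebo events and 50% of cholecalciferol events:
- placebo: 13.5/(13.5 + 270.75) = 4.7%
- cholecalciferol: 7.5/(7.5 + 270.75) = 2.7%

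An apparent benefit arises from exclusion alone.

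**6. Power, as distinct from bias (assumed losses).**
- Patients lost at random and equally in both arms, by the normal-approximation formula: 82.1% at 300 per arm, 80.1% at 5% loss, 77.9% at 10%, 73.0% at 20%.
- Event patients lost in equal proportion in both arms, by exact calculation for the chi-square test at 300 per arm: 86.4% with none lost, 70.9% if 30% are lost, 53.6% if 50% are lost. The 30% and 50% are purely illustrative. Because they apply equally to both arms, they show lost power and not bias.

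**The case against.** Several points on the other side have weight.

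- **Only missing primary data is expressly tied to exclusion from the evaluation.** For stopped or unblinded patients, exclusion is an inference: they leave, month-6 data are then absent, and 20c applies. Examiner exclusion is worded as a possibility in rare circumstances. This stands, and it limits the point to what the rules can do.
- **A reader might infer that a patient with a complication at week 6 who later dies or is unblinded is lost as an event.** The documents do not say so. The endpoint can be met at any time, and there are in-hospital and 6-week examinations, so such a patient's status may already be known. The text leaves it open.
- **A reader might also apply the cited range, "mortality rates from complications are variable (7–80" per cent, to the 15 placebo events to count events lost to death.** That is not supported. The range is literature-wide, nothing makes death a ground for exclusion, and these patients already have a complication that may have been recorded.
- **Removal for hypercalcaemia biases the result only if it also relates to complication risk.** That is correct, and neither link is quantified.
- **Imputation is planned, and a condensed article need not give a full analysis-population definition.** True, but the exclusion rule, the dismissal on unblinding and the limited exit follow-up are all stated rules. The sensitivity analysis softens the problem without changing the primary result.
- **Section 18b promises complete follow-up by telephone.** A call cannot establish an endpoint that needs inspection, palpation and auscultation.

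**Conclusion.** The point holds as a risk of bias. The article fixes a complete-case primary analysis and has exit rules that request no later wound assessment. Together they can remove randomised patients for reasons plausibly related to treatment or outcome. It would go too far to say that the primary result is an outcome-dependent subset, because the article gives no exclusion rates and does not say that data recorded before exit are discarded.

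The loss of power from modest random exclusion is small (82.1% to 77.9% at an assumed 10%). Possible bias with about 18 events matters more: at the planned event counts, five placebo patients with events take p from 0.004 to 0.046, and a sixth takes it past 0.05. These figures rest on the planned 5% and 1% rates and on assumed losses. The rules are worth correcting before analysis because the remedy is cheap and the number of events is small.

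**What to change.** - State that stopping the study drug or unblinding ends treatment or blinding, but not follow-up. Keep the scheduled 6-week and 6-month wound examinations for patients who still consent. Use the telephone contact in 18b to arrange these visits, not to replace the examination.
- Make the primary analysis all randomised patients who had sternotomy, by allocated arm, and report by arm how many were randomised but not operated on.
- Count as an event any complication meeting the endpoint definition and documented before stopping, unblinding or death.
- Replace the exclusion rule in 20c. Handle unknown primary status by the multiple imputation already planned, and report the complete-case result as the sensitivity analysis.
- Reconcile 20c with section 12, so that it is clear whether a patient with an incomplete assessment is missing or counted as free of complications.

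The cost is amendment wording and some effort to bring patients who have left treatment to visits already scheduled. There are two small downsides: off-treatment time dilutes the effect somewhat, and imputation of a rare event depends on its model when events are few.
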